### Hypotheses

Hypothesis 1. Participants in the MBTCC group will report significantly greater improvements at 8-week (T2), 6-month (T3), and 12-month (T4) follow-ups in regard to measures of the primary outcome of insomnia severity, compared with participants in the MBI-alone group, the TCC-alone group, and the SHE control group.Hypothesis 2. Participants in the MBI-alone group will experience significantly greater improvements than those in the SHE control group in the primary outcomes across time, in which the beneficial effects on insomnia severity will be mediated by rumination and psychological function.Hypothesis 3. Participants in the TCC-alone group will experience significantly greater improvements than those in the SHE control group in the primary outcomes across time, in which the promising effects on insomnia severity will be mediated by the arousal level and physical function.Hypothesis 4. The favourable effects of the MBTCC group on insomnia severity will be mediated by all the proposed mediators.

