### Data processing and analysis

The data will be analysed using SPSS version 26.0 on an intention-to-treat basis. To test the first study hypothesis, we will employ linear mixed models with restricted maximum likelihood estimation to test the individual growth model. This integrated random coefficient approach is usually conceptualized as a two-level model. Level 1, or the within-subject model, is the model used for repeated measures. Level 2, or the between-subjects model, is the model used for time-invariant variables between groups of individuals. The time factor, the grouping factor, and the interaction effect in mixed modelling will be examined. Additionally, the trend depicted in the least square mean plot will be evaluated to determine whether or not any trend-based differences exist between different groups. Hypothesis 1 would be supported if the models assessed and compared are fitted by using appropriate fit statistics. To test hypotheses 2 to 4, macro PROCESS SPSS and the bootstrapping approach will be used to assess the moderated mediation effects in the path model. Each mediator will be mean centred to form the interaction terms. The effects of covariates such as age or gender will be adjusted accordingly. The PROCESS macro is based on ordinary least squares regression. In addition, the mediating effect will be examined by data visualization techniques, such as Trellis coplot, also known as the conditional plot. Hypotheses 2 to 4 would be supported if any mediation effect exists.

The contents of the focus group interviews will be audiotaped and transcribed by a team of independent raters. Thematic analysis will be conducted with the help of the software NVivo (version 12) to store and manage the data. Coding and analysis will involve interpretative phenomenological analysis, which uses a bottom-up approach to determine the themes. Throughout the analysis, the codes will be identified from frequently used words or ideas in the transcripts. The codes will then be categorized into larger recurrent themes for further analysis. The research team will meet to discuss the significance of each theme and to triangulate the results with the quantitative findings.

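### Hypotheses 2 to 4 state plain mediation, but the planned test is moderated mediation with no moderator named and no deciding coefficient fixed

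*Protocol article*

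**What the plan says.** **Hypotheses (protocol article).** For the MBI arm, "the beneficial effects on insomnia severity will be mediated by rumination and psychological function". For the TCC arm, "the promising effects on insomnia severity will be mediated by the arousal level and physical function". For the combined arm: "The favourable effects of the MBTCC group on insomnia severity will be mediated by all the proposed mediators". Study aims 2 to 4 likewise speak only of mediating roles, and each is introduced as exploratory.

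**Data processing and analysis (protocol article).** The method given for the last three hypotheses is this: "macro PROCESS SPSS and the bootstrapping approach will be used to assess the moderated mediation effects in the path model". The next sentence adds: "Each mediator will be mean centred to form the interaction terms". Age and gender are mentioned only as covariates to adjust for. A graphical method is added for examining mediation, "such as Trellis coplot, also known as the conditional plot". The paragraph ends by counting Hypotheses 2 to 4 as supported when a mediation effect of any kind is found.

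**The concern.** Mediation and moderated mediation are different questions with different null hypotheses. Mediation asks whether the product of two paths, arm to mediator and mediator to outcome, differs from zero. Moderated mediation asks whether that product changes across levels of another variable. The hypotheses ask the first question and the analysis sentence names the second.

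This is more than one stray word, because the following sentence builds interaction terms into the model. The article does not say what each mediator is multiplied by. Once a product term is in the model, the mediator's own coefficient is conditional: it is the slope where the other variable equals zero. Centring the mediator does not change that. If the other factor is arm coded 0/1, for example, the mediator coefficient is the slope in the control arm only.

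At stake is whether three of the four hypotheses have a defined test. The same data set could support or fail to support a mediation claim depending on which of several quantities is read, and nothing in the article prevents that choice from being made after the results are seen.

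**Working it through.** **Plan's own figure.** None exists for this point. The powers of .86 and .97 under Sample size are given for a main effect and an interaction effect at effect size .25. They are not given for any mediation test, so there is nothing to reproduce.

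**Inputs from the article.** 180 evaluable participants in four arms, 180/4 = 45 per arm; 256 recruited, 256/4 = 64 per arm; OLS-based PROCESS with bootstrapping.

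**Inputs assumed.** Arm-to-mediator path a = 0.5 or 0.8 SD; mediator-to-outcome path b = 0.4, 0.5 or 0.6; direct effect c = 0.2; residual SD 1; no moderation. For orientation, the pilot table gives standardised differences from SHE of 0.51 (rumination, MBI), 0.41 (mental health, MBI), 0.52 (physical health, TCC) and 0.93 (hyperarousal, TCC), in absolute value. The article gives no values for b or c.

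**Quantities compared**, with X = arm, M = mediator, Y = ISI, W = a moderator:

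1. Simple mediation: M = aX + e, Y = cX + bM + e. Indirect effect = a·b.
2. Moderator on the second path: Y = cX + b1·M + b2·W + b3·M·W. Conditional indirect effect at W = w is a·(b1 + b3·w); index = a·b3.
3. Moderator on the first path: M = a1·X + a2·W + a3·X·W. Index = a3·b.
4. Arm itself as moderator: Y = cX + b1·M + b3·X·M. Treated-arm indirect effect = a·(b1 + b3); index = a·b3.

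If the mediator works alike for everyone, a3 = b3 = 0. Every index is then exactly 0, while the indirect effect is not: with a = 0.5 and b = 0.4, a·b = 0.5 × 0.4 = 0.20.

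**Simulation.** Two-arm contrast, 400 trials per setting, 500 percentile-bootstrap draws each. Percentage of trials whose 95% interval excluded zero:

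| n per arm | a | b | Simple a·b | Conditional, at moderator mean | Conditional, treated arm (arm as moderator) | Index (range over three placements) |
|---|---|---|---|---|---|---|
| 45 | 0.5 | 0.4 | 62.5 | 61.0 | 47.8 | 2.8–5.2 |
| 45 | 0.5 | 0.6 | 67.5 | 67.2 | 65.0 | 2.2–6.2 |
| 45 | 0.8 | 0.5 | 96.0 | 95.5 | 85.0 | 3.0–7.0 |
| 64 | 0.5 | 0.4 | 81.2 | 81.2 | 69.0 | 2.8–4.5 |
| 64 | 0.5 | 0.6 | 80.8 | 80.8 | 80.2 | 4.8–6.2 |
| 64 | 0.8 | 0.5 | 99.0 | 99.0 | 96.5 | 5.2–7.8 |

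The conditional effect at the moderator mean was computed with the moderator on the second path. Monte Carlo standard error is about √(0.05 × 0.95/400) = 1.1 percentage points near 5%, and √(0.625 × 0.375/400) = 2.4 points near 62.5%. The index column is therefore the nominal 5% plus noise, as it must be when the true index is zero. With no true mediation (a = 0, b = 0.5, 45 per arm), the simple test excluded zero in 7.8% of trials, so false positives do not explain its detection rates.

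**The case against.** A reader might infer that real mediation would be found only at about the false-positive rate, so that aims 2 to 4 would come out negative even when the mediators work. The document does not support that. Its decision rule asks whether any mediation effect is present, not whether an interaction is significant, and the index of moderated mediation is never mentioned. A model with product terms still yields conditional indirect effects. Read at the moderator mean, these lose almost nothing against the simple test. With arm as the moderator, the treated-arm effect loses up to about 15 points (62.5 − 47.8 = 14.7), which is still far from 5%.

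Other points also stand. An arm-by-mediator product is a recognised specification for mediation. The conditional plot is introduced as an additional display, not as the deciding test. Details such as the PROCESS model number are commonly left to a statistical analysis plan, so the lack of a named moderator would carry little weight on its own.

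None of this removes the mismatch. The article commits to a specific analysis that answers a question no aim or hypothesis asks. A later plan would have to contradict that commitment or bring in a moderator that the article does not mention. The decision rule does not close the gap either, because it names no coefficient, moderator level or contrast.

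**Conclusion.** The point holds as a mismatch between hypotheses and analysis, together with an undefined deciding quantity. For the same true, unmoderated mediation, the chance of declaring it runs from about 2–8% if the interaction or index is used, through about 48–99% for conditional indirect effects, to about 62–99% for simple indirect effects.

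The low figure describes one possible reading and is not the expected result of this plan. It does not depend on the assumed path sizes, because the true index is zero by construction. The other ranges do depend on them; a weaker arm-to-mediator path, such as the pilot's 0.41, was not simulated and would give lower detection.

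Severity is moderate. Aims 2 to 4 are worded as exploratory, and Hypothesis 1 on insomnia severity is tested separately by linear mixed models.

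**What to change.** In Data processing and analysis:

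- State that each of Hypotheses 2 to 4 is tested by the bootstrap confidence interval of the specific indirect effects it names, for the relevant active arm against SHE: rumination and psychological function for MBI, arousal and physical function for TCC, and all proposed mediators for MBTCC. Separate models per mediator or one parallel-mediator model would both match the hypotheses; the text should say which is used.
- Delete the word moderated and the sentence on centring and interaction terms. Alternatively, keep an arm-by-mediator term as a labelled sensitivity analysis. If moderation is really intended, name the moderator and add its hypothesis.
- Reword the closing rule so that it points to those intervals. At present it accepts any mediation effect, which is looser than Hypothesis 4, where all the mediators are claimed.
- Describe the conditional plot as descriptive.

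The cost is one rewritten paragraph, settled before the data are analysed. The data collected, the sample size and the software stay the same.

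### The rule that Hypotheses 2 to 4 are supported by any mediation effect contradicts the hypotheses, which require all named mediators and, for Hypotheses 2 and 3, superiority over sleep hygiene education (SHE)

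*Protocol article*

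**What the plan says.** The Hypotheses section of the protocol article states three mechanistic hypotheses.

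- **H2**, superiority: "Participants in the MBI-alone group will experience significantly greater improvements than those in the SHE control group in the primary outcomes across time". Mechanism: "the beneficial effects on insomnia severity will be mediated by rumination and psychological function".
- **H3**, superiority: "Participants in the TCC-alone group will experience significantly greater improvements than those in the SHE control group in the primary outcomes across time". Mechanism: "the promising effects on insomnia severity will be mediated by the arousal level and physical function".
- **H4**: "The favourable effects of the MBTCC group on insomnia severity will be mediated by all the proposed mediators". Taken with Study aims and the Mediators section, the proposed mediators are four: rumination, psychological function, arousal level and physical function.

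The Data processing and analysis section gives all three hypotheses one method, a bootstrapped path analysis: "To test hypotheses 2 to 4, macro PROCESS SPSS and the bootstrapping approach will be used to assess the moderated mediation effects in the path". It then gives them one criterion: "Hypotheses 2 to 4 would be supported if any mediation effect exists". The linear mixed model, which examines time, group and their interaction, is introduced there as the test of the first hypothesis only.

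**The concern.** A support rule should be met only when the hypothesis it serves is borne out. Here H4 says *all* and the rule says *any*. H2 and H3 join two mediators with *and*, and the rule accepts one. H2 and H3 also open with a claim of superiority over SHE, and the rule is silent on it.

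The trial's rationale is that mindfulness and Tai Chi act through different routes and that the combined programme uses both. H2 to H4 are where the plan tests this. Under the stated rule the report could call the mechanism hypotheses supported when a single pathway was found in each arm, or when a single-component arm showed no benefit over SHE. Accepting any one of several tests also raises the chance of a false claim of support.

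**Working it through.** **1. Rule against hypotheses.** The plan gives no figure to reproduce, so the texts are compared first.

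| | Hypothesis requires | Rule requires |
|---|---|---|
| H2 | MBI better than SHE on ISI; rumination and psychological function both mediate | one mediation effect |
| H3 | TCC better than SHE on ISI; arousal and physical function both mediate | one mediation effect |
| H4 | all four mediators mediate | one mediation effect |

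The rule does not imply the superiority clause. An indirect effect (arm to mediator, times mediator to ISI) can be found when the total effect of the arm on ISI is not significant. Nothing else in the article narrows the rule or adds the missing conditions.

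**2. Ceiling on false support for H4.** Assume no mediator is related to ISI, four independent tests, and 5% error for each. The Sample size section sets alpha at .05. The article states no level for the mediation tests, so 5% is an assumption there.

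- Any of four: 1 − 0.95^4 = 0.185.
- All four: 0.05^4 = 0.00000625.

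This is a ceiling. The test of a product reaches 5% only when the arm has a strong effect on the mediator.

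**3. A less extreme figure.** Inputs:

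- 180 / 4 = 45 per arm, from the Sample size section.
- MBTCC-versus-SHE pilot effects from Table 1 as arm-to-mediator shifts: −0.57 rumination, 0.48 mental health, −1.24 hyperarousal, 0.69 physical health. H4 names no comparator; SHE is assumed.
- No relation of any mediator to ISI.
- Four mediators in parallel, each path tested at 5%, and mediation declared when both paths are significant.

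Simulated probability that at least one mediator is declared: about 14 to 15%, whether the mediators are uncorrelated or correlated 0.5. Using a 95% Monte Carlo interval for the product in place of the bootstrap gives 13 to 15%.

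Smaller shifts lower it. The pilot MBI shifts (−0.51, 0.41, −0.44, 0.24) give about 7 to 9%. A shift of 0.25 on every mediator gives a few per cent (roughly 2 to 5%, depending on the test). With no shift it is below 1%.

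**4. One true mediator out of four.** With 80% power for the true one and the other three null:

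- Any: between 0.80 (the null tests never reject) and 1 − 0.2 × 0.95^3 = 0.83 (each rejects 5% of the time).
- All: at most 0.8 × 0.05^3 = 0.0001.

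This case shows the contradiction most clearly. H4 as written is false, yet the rule would declare it supported about four times in five.

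**5. Price of the strict rule.** With every mediator real, 80% power each and independence:

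- Two mediators: 0.8^2 = 0.64, before the superiority condition.
- Four mediators: 0.8^4 = 0.41.

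**The case against.** **The aims are exploratory.** Study aims 2 to 4 are worded as exploration, and H1, which carries the primary comparison, does not use this rule. That stands and lowers the severity. It does not remove the contradiction, because the article turns these aims into hypotheses and gives them a support criterion.

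**The rule can be read charitably.** A reader might infer that a mediator outside H2's list, such as arousal, would support H2. The aims and hypotheses name the mediators for each arm, so the rule can fairly be read as any of those named. The point does not need the more literal reading. Even the charitable one conflicts with *all* in H4, with *and* in H2 and H3, and with the SHE clause.

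**The SHE contrasts can be obtained.** A reader might infer that no analysis compares MBI or TCC with SHE. The mixed model covers four arms and can supply both contrasts. What is absent is their place in the rule for H2 and H3.

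**The size can be overstated.** Counting four mediators at three visits as 12 independent tests would give a far larger error rate than 18.5%. The plan states no separate mediation test per visit, and repeated measures on the same people are not independent, so such a figure has no basis here.

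**The pilot does not show which mediator would carry the rule.** It is tempting to infer from the large pilot effect on hyperarousal that arousal alone would satisfy H4. Table 1 gives no association between any mediator and ISI, and the pilot MBTCC arm had 10 participants. The pilot values serve above only as plausible arm-to-mediator shifts.

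**A fuller analysis plan may exist.** It could add detail, but this point is not about missing detail. The published rule conflicts with the published hypotheses, and a later document would either inherit the rule or depart from it.

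**Conclusion.** The contradiction is plain from the text and does not depend on any calculation. One of four mediators would support H4; one mediator would support H2 or H3; and neither H2 nor H3 would need its arm to beat SHE.

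The false-support figures are illustrations for H4. The 18.5% is an upper limit under independent 5% tests. The 14 to 15% assumes 45 per arm, SHE as comparator, the pilot MBTCC shifts and no mediator-to-ISI relation, and it falls as the shifts shrink.

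The defect concerns how mechanistic hypotheses are declared supported. It should be corrected before the mediation results are known, since a later change would look driven by the data. It ranks below the faults that must be fixed for the trial's main conclusion to stand, because the comparison in H1 is untouched.

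**What to change.** Replace the sentence with a rule that mirrors the hypotheses, for example:

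> H2 (H3) is supported if MBI (TCC) is superior to SHE on ISI in the mixed model and the 95% bootstrap intervals for both named indirect effects exclude zero in the hypothesised direction, at one pre-specified time point. H4 is supported only if the intervals for all four indirect effects exclude zero at that time point. If only some do, those mediators are reported singly as partial, exploratory evidence.

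The investigators should choose the time point now. Because every condition must hold, no alpha adjustment is needed within a hypothesis at that single time point. That would no longer be true if success at any visit were allowed to count.

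The change needs no new data or participants. Its real cost is that full support becomes harder to reach: about 41% for H4 and at most 64% for H2 or H3 under the assumptions in step 5. The Sample size section reports power only for the main and interaction effects, so the trial was not sized for this. That difficulty belongs to the hypotheses as stated. If the investigators regard it as too demanding, the consistent alternative is to weaken the hypotheses openly rather than keep a looser rule beneath them.

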## Discussion

MBIs and TCC are both perceived as mind-body interventions and share the common feature of a focus on breathing, but they may represent distinct approaches with different mechanisms and philosophical orientations. MBIs focus on stress management via changes in cognitive and behavioural responses and may therefore be conducive to treating rumination or psychological dysfunction. TCC, on the other hand, places a greater emphasis on physical health outcomes and the arousal-related physiological dimensions of sleep disturbance. Thus, *combining both MBIs and TCC has the potential to optimize improvements in sleep disturbance*. However, there is a dearth of evidence to guide clinical practice in regard to the best way to integrate these approaches. The current research study seeks to address this knowledge gap by investigating the combined effects of MBIs and TCC in the management of sleep disturbances.

This study has several potential limitations, including the risk of attrition and selection bias. In order to maintain the distinct benefit of randomization as a mechanism to prevent selection bias, an “as-randomized” analysis keeps participants in the group to which they were initially allocated. To avoid attrition bias, outcome data obtained from all participants are included in the data analysis, regardless of protocol adherence. That is, intention-to-treat analysis will be used as the ideal analysis strategy in this study. In addition, the study entails a long follow-up period. To achieve a high follow-up rate, we will ensure good communication between research personnel and participants, accessibility and convenience to nearby elderly community centres, effective communication channels, and appropriate incentives to continue and ensure that the study is of relevance to the participants.

Nevertheless, the present research project should determine the effects of an integrated MBTCC programme on sleep disturbances among Chinese older adults living in the community. The research findings can allow older adults or healthcare professionals to select appropriate practices. This will produce benefits, satisfaction, adherence, and sustainability in early interventions, which are potentially less costly and have fewer side effects. In addition, an evidence-based alternative intervention, as shown in this study, can help alleviate the burgeoning public health burden of sleep disturbances among older adults living in the community.

## Trial status

ClinicalTrials.gov ID: NCT05396092 (published on 24 May 2022)

The expected start date of recruitment: September 1, 2022

The expected end date of recruitment: April 18, 2025

## Data Availability

Any data required to support the protocol can be supplied on request. The datasets analysed during the current study and statistical code are available from the corresponding author on reasonable request, as is the full protocol.

## Abbreviations

CAM: Complementary and alternative medicine
MBIs: Mindfulness-based interventions
TCC: Tai Chi Chuan
MBTCC: Mindfulness-based Tai Chi Chuan
SHE: Sleep hygiene education
